## Abstract

**Background:**

Early reports indicate that COVID-19 may require intensive care unit (ICU) admission in 5–26% and overall mortality can rise to 11% of the recognised cases, particularly affecting the elderly. There is a lack of evidence-based targeted pharmacological therapy for its prevention and treatment.

We aim to compare the effects of a World Health Organization recommendation-based education and a personalised complex preventive lifestyle intervention package (based on the same WHO recommendation) on the outcomes of the COVID-19.

**Methods:**

PROACTIVE-19 is a pragmatic, randomised controlled clinical trial with adaptive “sample size re-estimation” design. Hungarian population over the age of 60 years without confirmed COVID-19 will be approached to participate in a telephone health assessment and lifestyle counselling voluntarily. Volunteers will be randomised into two groups: (A) general health education and (B) personalised health education. Participants will go through questioning and recommendation in 5 fields: (1) mental health, (2) smoking habits, (3) physical activity, (4) dietary habits, and (5) alcohol consumption. Both groups A and B will receive the same line of questioning to assess habits concerning these topics. Assessment will be done weekly during the first month, every second week in the second month, then monthly. The composite primary endpoint will include the rate of ICU admission, hospital admission (longer than 48 h), and mortality in COVID-19-positive cases. The estimated sample size is 3788 subjects per study arm. The planned duration of the follow-up is a minimum of 1 year.

**Discussion:**

These interventions may boost the body’s cardiovascular and pulmonary reserve capacities, leading to improved resistance against the damage caused by COVID-19. Consequently, lifestyle changes can reduce the incidence of life-threatening conditions and attenuate the detrimental effects of the pandemic seriously affecting the older population.

**Trial registration:**

The study has been approved by the Scientific and Research Ethics Committee of the Hungarian Medical Research Council (IV/2428- 2 /2020/EKU) and has been registered at clinicaltrials.gov (NCT04321928) on 25 March 2020.

## Background

World Health Organization (WHO) announced the coronavirus disease 2019 (COVID-2019) outbreak pandemic in the morning of 12 March 2020 [1]. At the time of writing this study protocol, there are more than 770,000 confirmed cases with 37,000 fatalities across 178 countries, according to the Center For Systems Science and Engineering (CSSE) at Johns Hopkins University, including 447 cases and 15 deaths in Hungary. The tendency predicts that the epidemic is far from its peak [2].

As often seen in the case of other epidemics, most cases can be asymptomatic or develop only mild symptoms and remain undiagnosed. Therefore, it is difficult to estimate the true incidence and the disease outcomes precisely [3, 4]. However, early reports indicate that it may require intensive care unit (ICU) admission in 5–26%, due to acute respiratory distress syndrome (ARDS) in 17–20%, and overall mortality can rise to 11% of the recognised cases, mostly affecting the elderly [5–8]. These numbers are comparable to the outcomes of earlier coronavirus epidemics [9, 10] and more severe than H1N1 pandemics in 2009 [11].

Significant efforts have been invested in research and development to re-target existing and discover new pharmacological treatments and preventive strategies against COVID-19 [12], as indicated by the number of submitted protocols of the currently recruiting randomised trials on ClinicalTrials.gov. Nevertheless, it must be noted that we lack evidence-based targeted pharmacological therapy for prevention and treatment alike [13]. None of the registered studies investigates the effects of lifestyle interventions in the prevention of poor outcomes in the COVID-19 epidemic. Advanced age and pre-existing comorbidities, such as cancer, cardiovascular disease, or diabetes mellitus, predispose to a more severe disease course and ICU admission [6, 14–16].

The high risk of being infected with COVID-19 as well as the social distancing and quarantining as primary recommendations for the suppression of virus transmission may generate a high level of anxiety and mental stress [17, 18]. In infected patients, better mental health might even have a positive impact on disease progression and survival [19, 20]. Therefore, efforts for better coping with the aversive psychological states caused by the COVID-19 outbreak have high importance in mental health resilience. The role of lifestyle factors and fitness in the severity of COVID-19 has remained unexplored except for two recent studies. The history of smoking is independently associated with disease progression (OR = 14.3, 95% CI 1.6–25.0) in a Chinese cohort of 78 patients [21]. Body mass index was > 25 kg/m^2^ in 88% of patients who died as compared to 19% in survivors in another Chinese cohort of 112 patients [22]. The latter seemingly contradicts the results of a very recent registry analysis of almost 100,000 participants where higher body mass index (indirectly, better nutritional status) proved to be neutral or even preventive although against non-COVID-19 upper airway infections [23]. These suggest that personalised lifestyle interventions via education or counselling could be beneficial for COVID-19 outcomes.

We did not find any complex lifestyle intervention aiming to improve outcomes of epidemic respiratory diseases by a comprehensive literature search. It is likely driven by the difficulty of organising clinical trials with lifestyle interventions. Most problems arise from the following circumstances of epidemics; (1) Exceptionally rapid response is required from the healthcare system. (2) Financial and human resources are often limited and re-routed to manage basic healthcare and public health measures. (3) Often only days are available to set up a trial. (4) The outcomes of the epidemics can only be guessed since the number of influencing variates is almost infinite. (5) We are unable to predict the number of affected cases within a period. (6) Efforts are invested in finding effective pharmacological targets rather in smaller samples. (7) Quarantine is often enforced when lifestyle factors are hard to control, and due to the restriction on personal interactions, informed consent, and data collection cannot be obtained in the usual way. (8) The legislation is not prepared to overcome the difficulties of fast track authorisation and organisation of clinical trials during epidemics. Unsurprisingly, no randomised clinical trial has been performed, to investigate the effects of a multicomponent preventive lifestyle intervention on the outcomes of COVID-19 epidemic.

Our main objective is to evaluate the effects of a personalised multicomponent lifestyle intervention aiming to improve the outcomes of COVID-19 infection in the population over 60 years in a randomised clinical trial. The main hypothesis of PROACTIVE-19 is that the personalised multicomponent lifestyle intervention reduces the rate of our composite outcome consisting of the need for intensive therapy, hospitalisation, and mortality in the COVID-19 population.

## Methods

### Design

The study protocol is structured following Spirit 2013 [24]. PROACTIVE-19 is a pragmatic, randomised controlled clinical trial with adaptive “sample size re-estimation” design. This design allows interim analyses and necessary modifications of the sample size of the ongoing trial to ensure adequate power [25].

### Legislative amendment and ethical approval

In Hungary, Act CLIV of 1997 on Health and Decree No. 23/2002 (of 9 May 2002) of the Minister of Health on Biomedical research on human individuals (as amended) stipulates the procedure for non-interventional investigation, according to which (1) the leader of the investigation or the investigator shall inform the subject both verbally and in writing, before obtaining the consent of the subject to participate in the clinical research, and (2) the participants’ informed consent shall be written. This Act and Decree would not have allowed commencing the clinical trial as it would have amounted to a criminal offence. Based on our request sent to the Prime Minister of Hungary to amend the Decree, the Government of Hungary issued Government Decree No. 63/2020 of 24 March 2020, according to which the new decree amends: (1) in addition to Section 159 of Act CLIV of 1997 on Health, subjects with full disposing capacities can be informed about the non-interventional investigation qualified as clinical research on coronavirus via means of telecommunications; (2) subjects may consent to participate in the clinical research through telecommunications; and (3) subjects may withdraw their consent through telecommunications.

Ethical approval: Scientific and Research Ethics Committee of the Hungarian Medical Research Council (IV/2428- 2 /2020/EKU).

### Patient and public involvement

We will perform the assessment and minor modifications in the structure and wording of data collection and the interventions based on the operators’ and participants’ feedback after testing the protocol on 100 potentially eligible subjects. Data of these subjects will not be recorded; only anonymous feedback will be given.

Patients were not included in the recruitment and conduct of the study. Immediately after publications, study results will be disseminated to the population above 60 years of age via the electronic media when, depending on which study arm will better, either general or personal lifestyle intervention will be delivered.

Our interventions do not impose a considerable financial burden on patients; therefore, such compensation will not be required. Volunteering patients, who helped us to test the interventions, claimed that the time and efforts needed to participate in the study and follow the recommendations (of the interventions) are entirely reasonable and acceptable.

### Study population

#### Inclusion and exclusion criteria

The inclusion criteria of our selective primary prevention programme are as follows: (1) age over 60 years (that is, high-risk individuals) and (2) informed consent to participate. The exclusion criteria are as follows: (1) confirmed COVID-19 (active or recovered), (2) hospitalisation at screening for eligibility, and (3) someone was already enrolled in the study from the same community/household (to avoid potential crosstalk between the study arms).

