#### Flow and timing

A toll-free phone number will be available for all interested in participation. By dialling this number, the participant will be informed about the trial through a pre-recorded voice message, including the study rationale, conditions of participation, the process of the study, and the information on data protection. Willing participants will be redirected to an available operator, who will ascertain eligibility. Following verbal consent and randomisation, the operator will obtain key personal information of the participants and all study-related information (Fig. 1). The allocation will not and cannot be concealed from the operator, but it will be concealed from everyone else (participants, caregivers, outcome assessors).

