### Outcomes

Based on literature data [5, 26], the primary endpoint will be defined as the composite of any of the following in COVID-19 cases (an accredited laboratory should verify positivity), the rate of:
ICU admissionsHospital admissions (longer than 48 h) for the following reasons:
Arrhythmia (causing hemodynamic instability and requiring continuous monitoring and/or cardiac support, as indicated by mean arterial pressure < 65 mmHg, and/or serum lactate > 2 mmol/L)ARDS (severe hypoxaemic respiratory failure indicated by a PaO_2_/FiO_2_ < 300 mmHg according to the Berlin definition) [27]Circulatory shock (the requirement of continuous vasopressor support to maintain mean arterial pressure ≥ 65 mmHg and/or serum lactate ≤ 2 mmol/L)Deaths

Secondary endpoints are the following:
The number of general practitioner visitsThe number of emergency, hospital, and intensive care admissionsThe length of hospitalisation and ICU stayThe number of organ dysfunctions and failures (central nervous system, cardiovascular, respiratory, renal, liver, haematological)The measurable lifestyle changes (including physical and mental health)The costs of care

The primary and secondary outcomes will be assessed upon the conclusion of the trial, at least 1 year after the enrolment of the last participant.

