### Sample size calculation, interim, and final analyses

The primary outcome is estimated to occur in 20% of COVID-19-infected cases (≥ 60 years of age) receiving the standard of care based on Chinese reports [5]. Due to the lack of data, we hypothesised that our intervention would result in a 50% risk reduction. Considering one interim analysis on efficacy (with the Pocock correction), 90% power, 5% alpha (superiority design, two-sided), a dropout rate of 20% [28, 29], and assuming 10% incidence of COVID-19 in the target population, the estimated sample size is 3788 (rounded up to 3800) subject per study arm. The calculation was performed by Stata (version 15, Philadelphia, the USA).

We plan to hold three interim analyses: the first for sample size re-estimation at 5% of the target sample size due to the dropout rate, the second for safety assessment at 10% of the target sample size, and the third for efficacy assessment and sample size reestimation at 50% of the target sample size. Early stopping will be executed if (1) safety concerns arise during the interim analysis; (2) the statistical power reaches at least 90% and *p* < 0.05 at the efficacy interim analysis (stopping for benefit); (3) the statistical power does not reach 10%, *p* > 0.05, and the event number does not reach the assumed 10% for the whole population at the efficacy interim analysis (that is, 380 events for the primary outcome; otherwise, the interim analysis is postponed and repeated when the event number reaches 380 events) (stopping for futility); and (4) the consequences of the pandemic make further recruitment or follow-up impossible (stopping for unfeasibility).

In the final analysis, the intention-to-treat analysis will be favoured over per-protocol (or “as-treated”) analysis. We expect a full dataset for the primary endpoint (since the Hungarian Ministry of Interior will provide these data). If for any reason, data will be missing for the primary outcome, we will use available case analysis. The “last observation carried forward” strategy will be followed to impute missing data for other outcomes measured during the study. Missing more than one consecutive interventions after the initial assessment or withdrawal of consent during follow-up results in the dropout of the patients unless hospitalisation is required in the meantime.

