## Discussion

Neither the worldwide climax of the COVID-19 pandemic can be foreseen nor the potential repeated outbreaks [2]. Although efforts of primary prevention (i.e. vaccine development) are promising, it is expected to take 12–18 months from now on [30]. Better lifestyle has its unquestionable advantages not only for infectious but also for common chronic diseases including diabetes mellitus, chronic heart failure or malignant tumours. Considering the recent low numbers of reported cases and the expected trajectory of the epidemic in Hungary, it seems that we are still on time to seek for personalised and easily available public health interventions applicable for the target population.

While in the USA, “remote” consent via telecommunication may be possible, the Hungarian laws have not allowed such initiatives until now. An outbreak imposes new challenges to the process of ethical approval [31]. Most importantly, the instant reaction of both the researchers and the ethical committees is essential, while preserving the validity of scientific content [32].

Based on the results of the current study, such strategies could be introduced in other countries. Lifestyle counselling is expected to reduce mental distress, smoking, and alcohol consumption; increase physical activity; and favourably change the body mass (along with the body composition). As the main results of all these, the interventions may boost the body’s cardiovascular and pulmonary reserve capacities, leading to improved resistance against the damage caused by COVID-19. Consequently, lifestyle changes can reduce the incidence of life-threatening conditions and attenuate the detrimental effects of the pandemic seriously affecting the older population.

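### Entry criteria exclude only confirmed COVID-19, so people with symptoms or a pending test can be randomised, which modestly dilutes the primary comparison towards no effect

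*Protocol article*

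**What the plan says.** The section on inclusion and exclusion criteria describes the trial as primary prevention ("The inclusion criteria of our selective primary prevention programme are as follows"). Inclusion requires age over 60 and consent. The exclusions are "confirmed COVID-19 (active or recovered), (2) hospitalisation at screening for eligibility", plus a person from a household or community already represented in the trial. No criterion concerns current symptoms or a pending test.

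Eligibility is settled by telephone under Flow and timing: "Willing participants will be redirected to an available operator, who will ascertain eligibility". No test at entry is described.

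Under Outcomes, "the primary endpoint will be defined as the composite of any of the following in COVID-19 cases (an accredited laboratory should verify positivity". No minimum interval between randomisation and infection is given. On timing, the section says only that "The primary and secondary outcomes will be assessed upon the conclusion of the trial", at least one year after the last enrolment. The statistical section adds that "the intention-to-treat analysis will be favoured over per-protocol".

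The mechanism is in the Discussion: "the interventions may boost the body’s cardiovascular and pulmonary reserve capacities, leading to improved resistance against the damage caused by COVID-19". Under Interventions, delivery is by calls that are weekly in the first month, fortnightly in the second and monthly thereafter. The Background concedes that "most cases can be asymptomatic or develop only mild symptoms and remain undiagnosed".

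**The concern.** The hypothesis is that changed habits, built up over repeated calls, reduce severe outcomes when infection comes later. Confirmed disease is a narrow screen for infection already present, and the Background accepts that cases can go undiagnosed. As written, a caller with fever and cough who awaits a result is eligible. If the result is positive a few days later and intensive care follows, that is a primary event after perhaps one call.

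Such cases carry the same weight as infections that follow months of counselling. Where they gain nothing, they move the relative risk towards 1. Power falls, and the effect in people who had time to change their habits is understated. A null or weak result would be harder to read.

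**Working it through.** **Inputs from the statistical section.** Control event rate 20% among infected participants; 50% risk reduction, so 10% in the intervention arm; 90% power; two-sided 5% alpha with the Pocock correction for one efficacy interim (nominal 0.0294 for two looks); 20% dropout; 10% incidence. Allocation is 1:1.

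**Step 1: reproduce the stated size.** Pooled-variance formula, no continuity correction, with z = 2.178 for two-sided 0.0294, z = 1.282 for 90% power and mean rate 0.15:

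- n = [2.178 × √(2 × 0.15 × 0.85) + 1.282 × √(0.20 × 0.80 + 0.10 × 0.90)]² / 0.10² = 303 infected per arm.
- 303 / 0.80 / 0.10 = 3787.5, so 3788 per arm. This is the article's figure.

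**Step 2: dilution.** Let f be the share of analysed COVID-19 cases already infected at randomisation. In the worst case they gain nothing and the rest have the assumed relative risk of 0.5:

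- RR = f × 1 + (1 − f) × 0.5; intervention rate p₂ = 0.20 × RR.
- Power = Φ{[(0.20 − p₂) − 2.178 × SE₀] / SE₁}, with SE₀ the pooled and SE₁ the unpooled standard error at 303 per arm.

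Example, f = 4%: RR = 0.52, p₂ = 0.104, SE₀ = √(0.152 × 0.848 × 2/303) = 0.0292, SE₁ = √[(0.16 + 0.104 × 0.896)/303] = 0.0289. Power = Φ(1.12) = 86.9%.

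| f (assumed) | RR | Power at 303 per arm | Subjects per arm for 90% power |
|---|---|---|---|
| 0 | 0.50 | 90.0% | 3788 |
| 2% | 0.51 | 88.5% | 3975 |
| 4% | 0.52 | 86.9% | 4163 |
| 6% | 0.53 | 85.2% | 4363 |
| 10% | 0.55 | 81.3% | 4813 |
| 20% | 0.60 | 69.5% | 6263 |

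**Step 3: a plausible range for f.** The article gives no accrual or infection curve. If infections fall evenly over 365 days, an assumed window of undetected infection of 7, 14 or 21 days gives 7/365 = 1.9%, 14/365 = 3.8% or 21/365 = 5.8%. So f is about 2-6% and the loss about 1.5 to 5 percentage points of power.

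**Step 4: what larger values require.** The design expects 2 × 303 = 606 analysed cases among 606 / 0.10 = 6060 retained participants. At f = 10%, about 61 cases would already be infected at entry, that is 61/6060 = 1.0% of retained participants. This is possible if enrolment meets a wave or ill people call preferentially, but nothing in the article establishes it.

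**Step 5: if early cases gain something.** With a 10% risk reduction (assumed) in the early cases, RR = 0.9f + 0.5(1 − f). Power is then 87.6% at f = 4%, 86.3% at 6% and 83.3% at 10%.

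**The case against.** The case for leaving the plan alone is substantial.

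- **The design is legitimate.** The trial is pragmatic, favours intention-to-treat, and names the effect of offering the intervention as a target under Strengths and limitations. Counting every randomised participant fits that. This stands, and the primary analysis should not change.
- **Early cases might benefit.** The Background suggests that better mental health could help people already infected, and mental health is one of the five domains. A reader might infer that counselling cannot alter these infections at all. The article does not support that, and zero effect is only the worst case.
- **The start of counting is not stated.** A reader might take it as given that events count from randomisation. No section says so. It is an inference from the lack of any lag, the favoured intention-to-treat analysis and assessment at trial end.
- **Undiagnosed infections do not all count.** Infections that are never laboratory-verified do not enter the endpoint population, so the Background remark does not measure the dilution.
- **Ill callers may be few.** The line is for people interested in the trial. The Safety section sends participants' COVID-19 concerns to a separate national helpline, and the article reports 447 cases in Hungary at the time of writing. This argues for a small f, but it makes no one ineligible.
- **Sample size re-estimation could recover a few points of power.** It could, but it would not restore a diluted relative risk.
- **Analysis detail belongs in the SAP.** This is fair for a breakdown of effect by time since randomisation, which is optional. It does not answer the eligibility point, because the criteria are set out in the article.

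**Conclusion.** The point holds as a modest design weakness. The listed criteria admit people who have symptoms or await a result, and the endpoint definition sets no interval that would keep their cases out. The consequence is dilution towards no effect, expected equally in both arms through randomisation. A reader might infer bias between arms or a raised false-positive rate, but neither follows.

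For infections present at entry, the loss is probably 1.5 to 5 points of power from 90%, with the relative risk moving from 0.50 to about 0.51-0.53. This rests on infections spread evenly over one year, a 7 to 21 day window and no benefit in these cases. Any benefit reduces the loss. A wave at enrolment or selective calling by ill people increases it, to 81% power at f = 10%.

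A reader might go further and cite the 70% power at f = 20%. Shares of that size would fit a wider group, namely everyone infected before counselling has had time to work. The article gives no figure for that group, and a screening question at entry would not address it.

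**What to change.** 1. In the inclusion and exclusion criteria, add a temporary exclusion for COVID-19-compatible symptoms or a pending SARS-CoV-2 test at the eligibility call. Defer these callers and contact them again once cleared. Silent incubation will still be missed, which is why the third change is needed.
2. Under Outcomes, state that endpoint counting starts at randomisation. Keep the all-randomised intention-to-treat analysis as primary.
3. Pre-specify one supportive analysis, by randomised arm, that leaves out cases first positive within a fixed window after randomisation (14 days, for example), applied identically to both arms.

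The cost is one or two screening questions, a few deferred callers, and slightly fewer events in the supportive analysis. That analysis needs only the dates of randomisation and first positive test.
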